### Specific Aims

**Primary aim 1:** Evaluate the effectiveness of Parent SMART+TAU versus TAU on proximal parenting outcomes. Hypothesis 1 is that, relative to those in TAU, parents receiving Parent SMART+TAU will exhibit greater improvements in parental monitoring and communication at 6, 12, and 24 weeks postdischarge from residential care.

**Primary aim 2:** Evaluate the effectiveness of Parent SMART+TAU versus TAU on distal adolescent substance outcomes. Hypothesis 2 is that, relative to those in TAU, adolescents whose parents receive Parent SMART+TAU will show greater reductions in the proportion of days substances were used outside a controlled environment and substance-related problems at 6, 12, and 24 weeks postdischarge from residential care.

**Secondary aim:** Evaluate the effectiveness of Parent SMART+TAU versus TAU on distal adolescent problem behavior outcomes commonly related to substance use: school problems, externalizing behaviors, sexual risk behavior, and criminal involvement. Hypothesis 3 is that adolescents whose parents receive Parent SMART+TAU will have greater reductions in a range of problem behaviors, including school truancy, externalizing behavior, risky sexual behavior, and criminal involvement at 6, 12, and 24 weeks postdischarge from residential, relative to adolescents in TAU.

**Exploratory aim**: Evaluate the extent to which change in parenting processes mediates change in adolescent substance outcomes. An exploratory hypothesis is that change in parenting processes (ie, communication, monitoring) at 6-weeks postdischarge from residential care will partially mediate primary adolescent substance use outcomes at 12 and 24 weeks.

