##### Parent Monitoring Questionnaire

The Parental Monitoring Questionnaire [37] is a 24-item youth and parent-reported measure containing three subscales. We will use the following versions of the subscales to assess dimensions of parental monitoring: child disclosure (parent report), parent solicitation (adolescent report), and parental control (adolescent report). Subscales were reliable in our pilot trial (α=.76-.87) and have been shown to correlate with adolescent mental health problems, deviant peer relationships, and family discord [37].

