##### Parent-Adolescent Communication Scale

The Parent-Adolescent Communication Scale [38] is an adolescent and parent reported measure with two subscales. The adolescent-reported version only will be used to assess positive (general family communication) and negative (problems with family communication) aspects of parent-adolescent communication. Subscales had good reliability (α=.71-.92) in our pilot [28] and have been shown to correlate with adolescent engagement in risk behavior [38].

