Primary aims 1 and 2 and the secondary aim compare trajectories of change using data from baseline, 6, 12, and 24 weeks follow-up on parenting processes, adolescent substance use, and adolescent problems, respectively. These aims will be evaluated in latent change score models with separate change effects for each of the adjacent time points [57]. For each aim (primary aims 1-2 and secondary aim), multiple outcomes are specified. For example, primary aim 1 specifies parental communication (two subscales) and parental monitoring (three subscales). Primary aim 2 includes days of substance use as well as problems related to substance use. A single latent variable at each time point will be used to define a composite outcome reflecting shared covariance among the multiple outcome indicators. Measurement invariance will be tested over time, and noninvariance will be assumed if necessary. “Point-in-time analyses” will be conducted to assess preliminary effects at 6 weeks and then at 12 weeks.

The exploratory aim examining potential mediators will be evaluated by bringing outcome models together in a single multivariate model. The exploratory hypothesis posits that positive changes in parenting processes at 6 weeks will be related to reductions in adolescent substance use and adolescent problems at 12 and 24 weeks. A bivariate change score model will evaluate change in parenting processes and change in adolescent substance use and related problems simultaneously and introduce a residual covariance term describing the association of change in parenting and change in adolescent outcomes. Time lagged regression coefficients will then be applied to test whether a change in parenting processes at 6 weeks leads to lower adolescent substance use and adolescent problems at 12 and 24 weeks. Examples of such an approach to evaluating mediation and moderation effects in the context of randomized trials can be found in McArdle and Prindle [60].

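### Hypothesis 1 claims gains in both monitoring and communication, but the plan tests one factor over all five subscales, so a positive result cannot support the two-part claim

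*Protocol article*

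**What the plan says.** Under Specific Aims, Hypothesis 1 is that "parents receiving Parent SMART+TAU will exhibit greater improvements in parental monitoring and communication at 6, 12, and 24 weeks postdischarge from residential care". The claim joins two named skills.

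The Data Analysis Plan (Overview) acknowledges the plurality: "For each aim (primary aims 1-2 and secondary aim), multiple outcomes are specified". It uses this aim as its example, listing two communication and three monitoring subscales. The next step is the rule at issue: "A single latent variable at each time point will be used to define a composite outcome reflecting shared covariance among the multiple outcome indicators". The only check on the factor is "Measurement invariance will be tested over time, and noninvariance will be assumed if necessary", which concerns visits, not arms or skills. The point-in-time analyses separate visits as well.

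The indicators come from two instruments and two informants. In the monitoring questionnaire, child disclosure is rated by the parent, while solicitation and control are rated by the adolescent. For the communication scale, "The adolescent-reported version only will be used to assess positive (general family communication) and negative (problems with family communication) aspects". The exploratory aim names communication and monitoring as the parenting processes that may mediate the effect on substance use.

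**The concern.** The planned model gives one arm coefficient per change interval for aim 1, and that coefficient belongs to whatever the five subscales share. The hypothesis needs two statements, one for each skill. A single coefficient cannot supply both unless the arm acts on the subscales only through the common factor, and the article plans no check of that.

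Two errors of interpretation become possible. A significant composite could be reported as improved monitoring and communication when only one of them moved. Conversely, a real benefit on one skill could be averaged away and reported as no effect. The mediation model carries the same ambiguity, because it could not say which parenting process transmits the effect.

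This is not a detail left to a separate analysis plan. The article fixes the outcome structure, and that structure does not match the hypothesis it is meant to test.

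**Working it through.** **Step 1. The plan's own figure.** Inputs from the article: 220 dyads, 1:1 allocation (110 per arm), type I error 0.05, 0.38 SD. I take the test as two-sided.
- Standard error of a standardised difference: √(2/110) = 0.1348.
- Power: Φ(0.38/0.1348 − 1.960) = Φ(0.858) = 0.805, which reproduces the stated 80%.
- Smallest observed effect that reaches significance: 1.960 × 0.1348 = 0.26 SD. So 0.38 SD is the effect detectable with 80% power, not a threshold for success.

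**Step 2. What one factor implies.** Write subscale j as y_j = λ_j·η + error, with η = β·arm + residual. The arm effect on subscale j is then λ_j·β, so all five effects are forced to be proportional to the loadings. If the true effects are not proportional, β is a weighted compromise, and the most strongly intercorrelated subscales get the most weight.

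**Step 3. Illustration with a one-factor model.** Assumptions, none given in the article: a true two-factor structure; loadings of 0.70 for solicitation and control, 0.75 for both communication subscales and 0.3 or 0.7 for child disclosure; correlation r between the skills of 0.3, 0.5 or 0.7. The true effect is 0 on monitoring and 0.5 SD on communication. Fitting one factor with arm as predictor to the population covariance by maximum likelihood gives these composite effects (SD):

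| Disclosure loading | r = 0.3 | r = 0.5 | r = 0.7 |
|---|---|---|---|
| 0.3 | 0.48 | 0.43 | 0.36 |
| 0.7 | 0.08 | 0.14 | 0.21 |

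The same truth gives a near-full or a near-null composite, depending mainly on one assumed loading. With 0.38 SD on both skills and a disclosure loading of 0.7, the same model gives 0.42 to 0.43 SD, so nothing is lost.

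**Step 4. Cross-check by weighting.** Standardise the five subscales and assume a within-skill correlation of 0.6 and a between-skill correlation of 0.3. The variance of their sum is 5 + 1.2 + 3.6 + 3.6 = 13.4, so its SD is 3.661.
- Communication only, 0.38 SD: 0.38 × √(2 + 1.2) / 3.661 = 0.186 SD on the unit-weighted composite. Power is Φ(0.186/0.1348 − 1.960) = 0.28, against 0.80 for a direct communication test.
- Monitoring only, 0.6 SD: 0.6 × √(3 + 3.6) / 3.661 = 0.421 SD. Power is 0.88 with unit weights and 0.98 with factor weights, with no communication effect at all.

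For a 0.38 SD effect on one skill, with within-skill correlations of 0.5 to 0.7 and between-skill correlations of 0.1 to 0.5, keeping only pairs where the between-skill value is the lower:

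| Effect on | Unit weights: SD (power) | Factor weights: SD (power) |
|---|---|---|
| Communication only | 0.17–0.21 (0.24–0.33) | 0.01–0.14 (0.03–0.18) |
| Monitoring only | 0.25–0.30 (0.44–0.60) | 0.27–0.38 (0.52–0.80) |

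**Step 5. Power for the two-skill claim.** With a true effect of 0.38 SD on each skill and each tested at 0.05, the chance that both are significant is 0.805² = 0.65 if the two estimates are uncorrelated. By the bivariate normal it is 0.67, 0.69 and 0.72 at correlations of 0.3, 0.5 and 0.7. Requiring a significant composite first costs nothing further if the composite weights the two skills equally: when both z values exceed 1.96, so does (z₁ + z₂)/√(2 + 2ρ). With a latent factor as the gate, these figures are approximate upper values.

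Steps 3 to 5 treat a single visit contrast without dropout. They are not a full latent change score model.

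**The case against.** A single composite has a legitimate purpose: one test and no multiplicity. Much of the article also speaks of parenting as one construct. The abstract refers to parenting skills, aim 1 to proximal parenting outcomes, and the mediation model is bivariate. Hypothesis 1 could be read in that spirit. This stands, and it is why the composite need not be given up; it does not turn one coefficient into evidence on two named skills.

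The scenarios above are also extreme. The pilot reported gains in both skills. In the six cells of the first table the one-factor model fits badly (population RMSEA about 0.13 to 0.21), which routine output would show. This too stands, and the figures should be read as illustration. The article does not say what would follow from poor fit.

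A reader might infer several stronger points that the document does not support:
- That a one-skill effect will be lost. A monitoring-only effect can keep almost all its power (up to 0.80).
- That child disclosure, the only parent-rated score, will hardly count. That depends on cross-informant agreement, which is not given, and the article gives a reason for its choice of informants.
- That the intervention trains the two skills separately. The Online Parent Skills Program and Coaching Sessions sections assign the same four techniques to opposite skills, so neither can be relied on here.
- That no other evidence on the skills is collected. The family assessment task yields blind-rated monitoring and communication scores under aim 1. The article places them in no stated analysis, so they do not close the gap.
- That two required primary factors must replace the composite. That would lower the power of the primary analysis and is not needed.

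**Conclusion.** The concern holds as a mismatch between hypothesis and test. As written, aim 1 yields an arm effect on one shared factor, and the article states no test of monitoring or of communication. A significant result would support improvement in a general parenting-skills construct, not in each skill.

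This conclusion is logical and needs no assumed numbers. The size of any dilution does: 0.08 to 0.48 SD for a true 0.5 SD effect on communication alone, on assumed loadings and correlations, and little or none if both skills respond together. The composite test is not invalid and its stated power is correct. What needs repair is the claim that may be drawn from it.

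**What to change.** - Keep the single latent composite as the primary aim 1 test.
- If it is significant, fit two correlated factors per visit, monitoring (three subscales) and communication (two subscales). Test the arm effect on each at 0.05, and conclude that both skills improved only if both tests are significant.
- Otherwise, word the conclusion as an effect on a single parenting-skills construct.
- Report the two skill effects with confidence intervals whatever the composite shows.
- Add a supporting version of the exploratory mediation model with the two factors entered separately.

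This costs some analysis-plan wording and a slightly larger model, with no new data. The composite test and its power are unchanged. The plan should state openly that power for the two-skill claim is only about 0.65 to 0.72 at true effects of 0.38 SD each, before dropout.

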**Objective:**

This protocol paper describes a fully-powered randomized controlled pragmatic effectiveness trial of Parent SMART as an adjunct to residential TAU. We hypothesize that families who receive Parent SMART will demonstrate greater improvements in parenting skills, reductions in adolescent substance use, and reductions in adolescent problem behaviors relative to families that receive residential TAU. We will test the exploratory hypothesis that reductions in adolescent substance use will be partially mediated by improvements in parenting skills.

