## Methods

### Study Design and Ethical Considerations

Parent-adolescent dyads will be assigned to receive either residential TAU or Parent SMART+ residential TAU on a 1:1 schedule using a two-arm, parallel-group, randomized trial design. The Brown University Institutional Review Board has approved all study procedures described herein (ID# 2006002748). The study is registered in clinicaltrials.gov (NCT05169385). The timing of key study elements, including randomization and parent-adolescent assessments, is depicted in Table 1.

**Table 1 table1:** Timing of key protocol elements.

		Residential treatment					Postdischarge period		
Timepoint		Enrollment	Baseline assessment	Allocation	Residential stay (2-45 Days)	6 weeks		12 weeks	24 weeks

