#### Power

The study’s primary and secondary aims were specifically powered to detect small to medium effect sizes on the Time*Condition interactions, based on: (1) the effect sizes detected in our pilot trial, which were small to medium in size, and which matched the proposed population in terms of severity; and (2) the effect sizes of the online parenting program on parenting processes detected in prior clinical trials, which were medium to large [24,32,33]. With a sample size of 220 dyads, we will have 80% power to detect a 0.38 standard deviation effect size or larger with a type I error risk of .05.

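### The only test named for the exploratory mediation aim is the lagged parenting-to-outcome coefficient, which by itself does not test mediation of the Parent SMART effect

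*Protocol article*

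**What the plan says.** The hypothesis appears in three places in the protocol article, and the last differs from the first two.

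- Abstract, Objective: the exploratory hypothesis is that "reductions in adolescent substance use will be partially mediated by improvements in parenting skills".
- Specific Aims, exploratory aim: parenting change at 6 weeks "will partially mediate primary adolescent substance use outcomes at 12 and 24 weeks".
- Data Analysis Plan, Overview: the statement of this aim "posits that positive changes in parenting processes at 6 weeks will be related to reductions in adolescent substance use and adolescent problems", both measured at the two later visits. Treatment condition is not mentioned.

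The same part of the Overview describes the analysis. The outcome models are joined into one multivariate model. A bivariate change score model will "introduce a residual covariance term describing the association of change in parenting and change in adolescent outcomes". Then comes the test: "Time lagged regression coefficients will then be applied to test whether a change in parenting processes at 6 weeks leads to lower" substance use and problems at the later visits. The article presents this as a way of evaluating mediation and points to a methods source for examples. It names no indirect effect, no interval or test for one, and no condition that Parent SMART must first have changed parenting.

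The Power section covers the other aims only: "The study’s primary and secondary aims were specifically powered to detect small to medium effect sizes on the Time*Condition interactions".

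**The concern.** Mediation of a randomised treatment needs two links: condition changes parenting (path a), and parenting change then alters the outcome (path b). The named coefficient is path b. It measures how parenting and later substance use move together, and it can differ from zero in both arms when condition has done nothing to parenting.

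The article gives reason to expect that. Its abstract treats parental monitoring and communication as already established predictors of adolescent use and relapse. A significant lagged coefficient could therefore simply reproduce known background association.

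At stake is the trial's statement about mechanism. The section on strengths and limitations presents the examination of putative mediators as a step beyond testing effectiveness, so a mechanism result is likely to be reported and should rest on a test that addresses it.

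**Working it through.** **Step 1. Reproduce the plan's own figure.** Dyads are randomised "on a 1:1 schedule using a two-arm, parallel-group, randomized trial design", so 220 dyads give 110 per arm. The Power section states 80% power for 0.38 SD at a type I error of .05. Sidedness is not stated; I take two-sided.

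- n per arm = 2 × ((1.960 + 0.842) / 0.38)² = 108.7, rounded up to 109 (218 in total).
- Detectable effect at 110 per arm = 2.802 × √(2/110) = 0.378 SD.
- Power at 110 per arm is 80.5% by the normal formula and 80.1% by the t test.

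The stated figure reproduces. No figure is given for the mediation aim, so there is nothing further to reproduce.

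**Step 2. How often is the named test significant when path a is zero?** Take M as parenting change and Y as later outcome, each with SD 1 within arm, and no direct effect of arm. Test b two-sided at .05 in a regression of Y on M and arm. The noncentrality is

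λ = b / √(1 − b²) × √(220 − 3),

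and the rejection probability is approximately Φ(λ − 1.96). For b = 0.20, λ = 0.2041 × 14.73 = 3.01, and Φ(1.05) = 0.85. Only the size of b matters here, not its sign.

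**Step 3. Compare with a test that needs both paths.** With a = 0, path a is significant 5% of the time. Treating the two tests as independent, both are significant in about 0.05 × (probability from step 2).

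The simulated columns come from 10,000 simulated trials of 220 dyads per setting. The last column sets a = 0.38 SD, borrowed from the Power section.

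| Assumed b | λ | Named test, a = 0: formula | Named test, a = 0: simulated | Both paths, a = 0: formula | Both paths, a = 0: simulated | Both paths, a = 0.38: simulated |
|---|---|---|---|---|---|---|
| 0.10 | 1.48 | 31.6% | 31.5% | 1.6% | 1.6% | 25.5% |
| 0.20 | 3.01 | 85.2% | 84.8% | 4.3% | 4.1% | 68.8% |
| 0.30 | 4.63 | 99.6% | 99.5% | 5.0% | 5.0% | 80.3% |

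Formula and simulation agree. With b = 0 as well as a = 0, the named test rejects in 5.0% of simulated trials, so it is a valid test of its own null hypothesis. That null is the absence of a lagged association, not the absence of mediation.

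**Step 4. Set the text side by side.** The Specific Aims ask whether parenting change carries an effect of condition to substance use. The Overview asks whether parenting change is related to later outcomes. Steps 2 and 3 show that the answers can diverge widely. The Overview also extends the outcomes to adolescent problems, whereas the Specific Aims limit mediation to the primary substance use outcomes.

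**The case against.** The strongest reply is that the treatment path is already in the analysis. The models being joined are those for the primary and secondary aims, whose purpose is to compare arms. Joining them most naturally brings in the effect of condition on parenting, and calling the covariance residual suggests that the change scores are already regressed on something. The effect on parenting is itself a primary hypothesis, so a null result there would be visible. This is a condensed article, and the interval method for an indirect effect commonly belongs in an analysis plan that is not shown. The cited methods source may also supply the missing step.

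Much of this stands. A reader might infer that mediation is tested by the lagged coefficient alone, with no information on treatment anywhere in the model, and that the trial would therefore claim mediation even if Parent SMART left parenting unchanged. The documents do not support that. The joint model probably contains the arm effects, and no sentence says that mediation will be declared on the lagged coefficient whatever primary aim 1 shows. Nor is a zero effect on parenting the expected case, since the pilot reported improvements in monitoring and communication.

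What remains is more than missing detail. The article states a hypothesis and a test in its analysis section, and neither matches the mediation hypothesis in its aims. Nothing in the text joins the two paths into one inference. An unseen analysis plan would have to correct this wording, not merely add to it.

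**Conclusion.** The point holds in a limited form: the one test named for the exploratory aim does not test the mediation hypothesis set out in the Specific Aims. With no arm effect on parenting, it would be significant in roughly 31% to 99% of trials at 220 dyads for lagged associations of 0.10 to 0.30. A test needing both paths would be significant in about 5% or less.

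These percentages are the power of a test of path b. They would become rates of false mediation claims only if the lagged coefficient were read by itself as evidence of mediation, which the wording permits but does not prescribe. They rest on assumed values of b, complete data on all 220 dyads, and single observed scores in place of the latent change model.

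The aim is labelled exploratory, and no power is claimed for it. No primary or secondary conclusion is affected. The change is still worth making because it is nearly free and the mechanism question is one the article emphasises.

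**What to change.** In the Data Analysis Plan, Overview, define the mediation test as the indirect effect of condition through 6-week parenting change on the 12- and 24-week substance use outcomes. Estimate it in the joint model as the product of two paths: condition to 6-week parenting change, and 6-week parenting change to later outcome, with adjustment for arm and for baseline parenting and substance use. Judge it by a bootstrap or Monte Carlo interval for the product, or by joint significance of both paths. Any of these is acceptable, provided that one is named in advance. Report the lagged coefficient by itself only as an association.

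In the same edit, restore the mediation wording of the hypothesis and reconcile whether adolescent problems are among the mediation outcomes.

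The second path is not randomised even after this change, so the result still depends on adequate adjustment and should be described accordingly. The cost is about one sentence of protocol text and a small extra analysis, with no new data and no change to the sample size.
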